### Participants

#### Eligibility

The inclusion criteria are summarized in Table 1. It is noteworthy that breast, prostate, and colorectal cancer diseases were selected, as they are the most common cancers in Portugal, with both sexes included [78]. Completion of primary treatments was also considered to minimize the impact of cancer treatment on biological markers, also considering that psychological distress may still be present in people who have had cancer, regardless of survival stage (at least up to 5 years) [79].

**Table 1 Tab1:** Eligibility criteria

Inclusion	Exclusion
• Age between 18 and 65 years old* • Diagnosis of breast, prostate, or colorectal cancer (cancer stage I to III) • Primary cancer treatments completed between 3 months to 5 years previously (ongoing hormonal therapy will be included) • Experience of significant distress at the time of inclusion (DT ≥ 4) • Willingness to accept randomization to one of the two study conditions and participation in the intervention and data collection for the duration of the study • Ability to speak, read, and write in Portuguese and literacy to autonomously complete the self-report measure • Sufficient digital literacy and access to a device (e.g. smartphone; tablet; computer) with a camera, microphone, and internet	• Concurrent diagnosis of severe psychiatric condition(s) (e.g. bipolar disorder; psychosis; substance abuse; suicidal ideation) • Concurrent diagnosis of autoimmune disorder • Current use of antipsychotics • Current use of anti-inflammatory medication (e.g. corticotherapy) • Ongoing trastuzumab therapy • Participation in a structured mindfulness programme (e.g. MBCR; MBCT; MBSR) in the past 5 years • Currently attending psychological consultation • Being pregnant or breastfeeding

*Note*. *DT* distress thermometer, *MBCR* mindfulness-based cancer recovery, *MBCT* mindfulness-based cognitive therapy, *MBSR* mindfulness-based stress reduction. *This age criterion was considered due to other study of the MindGAP project in which healthy blood donors reporting low psychological distress will be compared with distressed participants diagnosed with cancer for a better characterization of the CNS-EVs. This characterization is important given that CNS-EVs are a novel approach in both healthy and clinical groups. As blood donors are aged between 18 and 65 years, the same criterion was applied to the participants diagnosed with cancer to have a closer age match between groups

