#### Sample size estimation

Because no previous study has examined circulating EVs in relation to MBIs and cancer, we could not use a specific effect size in estimating the sample size. Nonetheless, a recent systematic review examining the effects of Internet-based MBIs on psychological distress (anxiety and depression) found a median Cohen’s *d* value between 0.38 and 0.42 for the other primary outcome, psychological distress [14]. By using G*Power-3.1 statistical software [82] and considering repeated-measures ANOVA related to within-between interaction (group × time interaction), with an alpha significance level of 0.05 and an effect size of 0.38 (as calculated in [83]), a sample of 84 participants would allow for a power of 0.80. Additionally, previous studies showed dropout rates ranging from 12.1 to 32% for the intervention group and from 6 and 17.4% for the control group, when considering the period immediately following the intervention [23, 32, 40, 47, 49, 52, 84]. At follow-up, dropout rates were about 30.8% in the intervention group and 19.6% in the control group [52]. Considering the highest dropout rate (32%), 27 participants should be added to the estimated sample, resulting in a minimum of 111 participants to be included in the study.

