### Assignment of intervention

#### Allocation

Participants will be randomly assigned to one of the two arms: MBCT or TAU groups (1:1 allocation ratio). Randomization blocks will be created using informatic tools and the entire process will be overseen by an investigator who will not be directly involved in the intervention or assessments. This investigator will inform the research team of the final allocation of each participant.

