### Statistical methods

Screening data for errors and missing values is the first step in the data analysis plan. Missing data will be managed and avoided during the data collection by using mandatory fields in the online surveys and retrieving the data from participants when possible. Data from participants who completed fewer than 4-weekly online MBCT sessions will not be considered further, as four sessions were set as the minimum number required for participation [14].

For each group (MBCT and TAU), a summary of baseline sociodemographic and health data will be provided, including number and percentages, mean, standard deviation, median, first and third quartiles, minimum and maximum. Using the sociodemographic and health data, as well as the primary and secondary measures, comparisons will be made between groups to examine whether there are differences between groups at baseline. Similarly, differences at baseline between participants who will complete the study and those who will drop out will be examined. The presence of differences in variables may warrant the need to examine and/or adjust for their influence on outcome changes in the primary analyses. This summary also presents the within-group effect sizes (Cohen’s *d*—equation 11.10, from [135]) for each outcome across time (i.e. T1 to T2; T1 to T3; T1 to T4; T1 to T5).

The total scores of each primary and secondary measure will be used as outcomes in multiple linear mixed models (LMMs). Each model will include the interaction between group and time, while participants will be treated as a random effect. The visual inspection of Q-Q plots will be conducted to check the normal distribution of residuals. Examination of factors such as sex, type of cancer, and cancer stage will be approached by running separate models for each factor. LMM analyses can be employed using, for instance, lmer4 [136] and lmerTest [137] in R software [138].

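### Sex and cancer type are to be examined in separate models, although only colorectal participants can tell the two apart, so a difference in one could be read as a difference in the other

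*Protocol article*

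**What the plan says.** Table 1 of the protocol article (Eligibility) admits participants with this criterion: "Diagnosis of breast, prostate, or colorectal cancer (cancer stage I to III"). The text above it explains the choice: "breast, prostate, and colorectal cancer diseases were selected, as they are the most common cancers in Portugal, with both sexes included".

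Statistical methods describes a linear mixed model for each primary and secondary measure: "Each model will include the interaction between group and time, while participants will be treated as a random effect". Further factors are then handled by one rule: "Examination of factors such as sex, type of cancer, and cancer stage will be approached by running separate models for each factor". The section does not say whether a factor enters as a main effect, as an interaction with group and time, or both.

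The only other provision on covariates is conditional. It follows the comparisons of the arms at baseline and of completers with dropouts: "The presence of differences in variables may warrant the need to examine and/or adjust for their influence on outcome changes in the primary analyses". No section puts sex and cancer type in one model, limits the sex comparison to colorectal cancer, or warns that the two factors overlap.

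**The concern.** Two of the three eligible cancers nearly fix the participant's sex. In a model with sex but not cancer type, the women are the breast participants plus some colorectal participants, and the men are the prostate participants plus the other colorectal participants. The sex term is then largely a contrast of breast with prostate cancer.

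The overlap works in both directions. Suppose the treatment effect differs by sex by an amount d and not by cancer type. Breast participants (women) and prostate participants (men) then differ by the whole of d, and the cancer-type model would report it as a cancer-type difference.

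What is at stake is the reading of the factor examinations. A report could say that MBCT works differently in women and men when the data cannot distinguish that from a difference between cancers.

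**Working it through.** The plan gives no figure for this point, so none can be reproduced. The check asks how large a false sex difference would be under stated assumptions.

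**Inputs**
- From Sample size estimation: N = 111 ("resulting in a minimum of 111 participants to be included in the study").
- From Allocation: two arms, 1:1.
- Assumed, not in the document: breast all women, prostate all men, colorectal half women; case mixes as in the table; true MBCT effect of 0.50 SD in breast, 0.25 in colorectal and 0 in prostate; no true sex effect; one change score with SD 1 instead of the full mixed model; nobody lost.

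**Step 1: spurious sex-by-arm difference.** With shares b (breast), p (prostate) and c (colorectal):

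- effect in women = (0.50b + 0.25c/2) / (b + c/2)
- effect in men = (0·p + 0.25c/2) / (p + c/2)

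For 70/10/20: women (0.350 + 0.025)/0.80 = 0.469; men 0.025/0.20 = 0.125; difference 0.344.

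**Step 2: its standard error.** With a share w of women and equal arms, SE = 2 / √(111·w·(1 − w)). For 70/10/20, w = 0.80, so SE = 2/√(111 × 0.16) = 0.475.

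**Step 3: standard error of the clean contrast.** Within colorectal participants only, four equal cells of 111c/4 give SE = √(16/(111c)). For c = 0.20 this is √(16/22.2) = 0.85.

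| Mix b/p/c (%) | Spurious difference (SD) | SE of sex-only contrast | Ratio | SE within colorectal |
|---|---|---|---|---|
| 70/10/20 | 0.344 | 0.475 | 0.72 | 0.85 |
| 60/20/20 | 0.381 | 0.414 | 0.92 | 0.85 |
| 80/10/10 | 0.402 | 0.532 | 0.76 | 1.20 |
| 50/25/25 | 0.367 | 0.392 | 0.94 | 0.76 |

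**Step 4: wider assumptions.** With mixes from 33/33/33 to 80/5/15 and women making up 30 to 60% of colorectal participants, cancer type explains 58 to 81% of the variance of sex. Take breast and prostate 1 unit apart, with colorectal midway: the sex-only model shows 0.58 to 0.77 units. If only colorectal cancer differs, the leak is 0.04 to 0.62 in size, depending on the mix.

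**Step 5: how often it would be declared.** Simulations used N = 111, a true sex effect of 0, 45% women in colorectal, a breast–prostate difference of 0.5 SD, and mixes 60/20/20, 50/25/25 and 33/33/33. The group-by-sex test rejected in 14 to 15% of runs, against a nominal 5%. Where cancer type shifted the change score equally in both arms, the sex term rejected in 42 to 44%.

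**Step 6: which model removes it.** Arm is randomised, so the sex-by-arm term is unrelated on average to a cancer-type main effect, and adding that main effect cannot absorb a type-by-arm difference. A large-sample simulation agreed: the spurious difference stayed at 0.33, 0.38, 0.42 and 0.36 for the four mixes in the table. With sex-by-arm and type-by-arm in the same model, the sex estimate centred near 0 (−0.04 to 0.00 in the Step 5 simulations). Its standard error was then about 1.8 to 2.3 times that of the sex-only model (for example 0.929 against 0.413 at 60/20/20), because only colorectal participants inform it.

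**The case against.** The strongest reply is that these are secondary factor examinations. The article states no hypothesis about sex, does not present these models as the primary estimates, and may leave their detail to an analysis plan that is not shown. All of that stands and keeps the point small. It does not remove it, because separate models are a stated rule and not an omission.

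It may also be said that the adjustment clause covers the problem. It does not. That clause is triggered by differences between arms, or between completers and dropouts. Sex and cancer type can be balanced on both and still be entangled with each other.

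A third reply is about size, and it stands. The spurious difference is only 0.7 to 0.9 of its own standard error, so under these assumptions the trial would usually declare no sex difference. A reader might set 0.34 to 0.40 SD beside the planning value ("with an alpha significance level of 0.05 and an effect size of 0.38") and conclude that the artefact is as large as the effect sought. The planning value belongs to the main comparison, not to a subgroup contrast, so the likeness means little.

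Other readings go further than the article allows:
- **Stage.** Nothing in the document ties stage to cancer type as sex is tied to it, so the same charge cannot be made for stage.
- **Lost precision.** With complete data, the group-by-time term is a within-participant contrast that time-invariant main effects leave unchanged. In three simulated trials (N = 112, four visits) its standard error was identical to five decimals with and without cancer type and stage.
- **Several competing treatment effects.** The base model is defined first and the factor examinations are described separately. The text does not offer them as alternative estimates of the treatment effect.

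**Conclusion.** The point holds as a minor one. As enrolled, sex and cancer type are separable only among colorectal participants, and separate models hide this. Any false sex finding is conditional: it needs a real difference by cancer type, which the document neither claims nor excludes, and a difference confined to colorectal cancer may leak very little. The sizes rest wholly on the assumed effects and case mixes.

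A reader might infer that the trial's main result is compromised. It is not: the randomised group-by-time comparison is untouched. Only the interpretation of the sex and cancer-type examinations is affected, and it is affected in both directions.

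**What to change.** Replace the stand-alone sex model in Statistical methods with one of two options:

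1. a comparison by sex within colorectal participants only; or
2. one model holding sex-by-group-by-time and cancer-type-by-group-by-time together, with their lower-order terms. Cancer type as a main effect only would not do.

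Report the sex result as an estimate with its interval. State that sex and cancer type are largely inseparable in this sample, and read the cancer-type model with the same caution.

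The cost is wording only, since sex and cancer type are already recorded. The downside is a visibly imprecise sex contrast: a standard error of about 0.8 to 1.2 SD for colorectal shares of 25% down to 10%. That imprecision reflects how little the sample can say about sex on its own.

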### Dissemination plans

The activities and results of the MindGAP project are updated on the project website [77] and disseminated on the project’s social networking platforms (Facebook, Twitter, LinkedIn, YouTube), which are linked on the project homepage. The public can interact with the research team through the former channels. The results of the study will be presented in scientific meetings and published in open-access journals. By the end of this study, it is planned to present the results to participants, healthcare professionals, and the community in an open session organized at IPOP. Social and traditional media platforms could also be used to reach a wider audience.

## Discussion

The motivation of this study is twofold: (1) to test the influence of MBCT practices on circulating CNS-derived EVs, investigated here for the first time; (2) and to further substantiate the impact of Internet-based MBCT on psychosocial and biological markers in an oncological context.

The use of CNS-derived EVs as tool for discovering biomarkers to support the psychosocial and biological changes that occur in the body following MBCT practices is a novel perspective never explored in the literature. The novel hypothesis presented here suggests that EVs may be involved in an important neurobiological mechanism of action underlying mindfulness interventions. Circulating CNS-EVs carry information to peripheral cells, and this information acts as instructions to these cells sent via mind-controlled events. In this hypothesis, EVs could lead to a further understanding of how mind-controlled activities can cause biological changes in the body.

There are challenges and limitations with this study that need to be acknowledged. First, the inclusion of participants with some level of digital literacy and access to digital devices and the Internet likely reflects sociodemographic characteristics, with younger and more educated participants being more mobilized [143]. Access to and use of information and communication technologies in Portugal is still closely associated with age and education, meaning that older and less-educated individuals are not as involved as other sociodemographic groups [144]. Accordingly, the results of this study may not apply to people with other sociodemographic characteristics. Nevertheless, this is an important step towards the development of digital mental healthcare services, whose underdevelopment in Portugal has been exposed by the current pandemic situation [145].

Moreover, despite the inclusion of specific types of cancer, which allows the formation of more homogeneous groups, as recommended in previous literature [14, 57], some individual characteristics and needs may be unconsidered. Accordingly, future studies could benefit from investigating other cancer types and stages (in treatment and palliative conditions [79]), exploring new ways to consider individual aspects [146], and including other outcomes (e.g. cognitive dysfunction, fatigue, pain) and possible associations with biological parameters [56].

Furthermore, given the novelty behind this study, the sample size of the objective primary outcome could not be adequately estimated for EV studies. Therefore, the current study may be underpowered to detect the effects of internet-based MBCT on circulating EVs. This problem could be compounded by difficulties with adherence and retention in this study, given the time and other specific demands of mindfulness practice [33]. With this concern in mind, specific strategies to mitigate dropouts were identified. Also, the qualitative methods proposed in this study might be useful in this regard.

The control data is obtained here by following TAU. This control condition was selected considering the available resources, the time window for conducting this clinical study, the previous use in online MBI studies [46, 48, 52, 53, 84, 89], and the desire for a year of follow-up comparison data (hence precluding a short waitlist period for the control group). We are aware that this approach does not allow control of specific (e.g. psychoeducational aspects) and nonspecific effects (e.g. group interactions and support; closer supervision; interaction with mental health professionals) [90]. An active control or even a comparison with another established intervention would be preferable, if possible [13, 90]. However, passive control conditions have been the most common in digital MBI research to date. As the field evolves, active control conditions are likely to become more common, as suggested by studies comparing face-to-face MBIs with Internet-based MBIs [31, 41, 42, 54, 84, 89] or studies using psychoeducational intervention as a comparison [32, 40].

Considering the challenges and limitations discussed earlier, it is important to say that not all scenarios are predictable. Therefore, the possibility of overcoming the challenges by adopting new or adapted strategies that may prevent the difficulties encountered throughout this study is anticipated, in a manner that provides valuable insights into health-related and psychosocial gains fostered by internet-based MBCT in an oncology context.

Overall, it is expected to confirm and clarify the role of CNS-EVs in altering the biochemical operation of peripheral cells in response to mind-related activities, while monitoring the extent of these changes in a wide range of subjective and objective parameters. This mechanism may open unprecedented opportunities to understand how the mind may interact with the body, in what quantitative dimension, and also provide tools for a mind-controlled activity that may benefit health.

## Trial status

The unique protocol ID is IPO/PI134b and the ClinicalTrials.gov Identifier is NCT04727593 (date of registration: 27 January 2021; date of record verification: 6 October 2021; https://clinicaltrials.gov/ct2/show/NCT04727593). The first wave of recruitment began on February 2021 and it is expected to continue until October 2022. The anticipated study completion date is March 1, 2023.

## Data Availability

This study was submitted and analysed by the IPOP’s data protection officer (Ref. – 137/2020). The final trial dataset will only be accessed by the researchers involved in the study. Data will not be publicly available. Nonetheless, some data will be shared with other partners of the MindGAP project and might be made available to other researchers upon reasonable request to the research team.

## Abbreviations

ACTH: Adrenocorticotropic Hormone
BaSIQS: Basic Scale on Insomnia Complaints and Quality of Sleep
CA: Cancer Antigen
CCI: Client Change Interview
COPE: Committee on Publication Ethics
CORE-OM: Clinical Outcome Routine Evaluation - Outcome Measure
CNS: Central Nervous System
CRP: C-Reactive Protein
DASS-21: Depression, Anxiety Stress Scales-21
DSM: Diagnostic and Statistical Manual
DT: Distress Thermometer
ERQ: Emotion Regulation Questionnaire
EVs: Extracellular Vesicles
FCR-7: 7-item Fear of Cancer Recurrence
FFMQ: Five-Facet Mindfulness Questionnaire
FTND: Fagerström Test for Nicotine Dependence
HPLC: High-Performance Liquid Chromatography
ICD: International Classification of Diseases
IFN-γ: Interferon Gamma
IFN: Interferon
IL: Interleukin
IPAQ-SF: International Physical Activity Questionnaire - Short Form
IPOP: Instituto Português de Oncologia do Porto (Portuguese Oncology Institute of Porto)
LMM: Linear Mixed Model
MBCR: Mindfulness-Based Cancer Recovery
MBCT: Mindfulness-Based Cognitive Therapy
MBIs: Mindfulness-Based Interventions
MBSR: Mindfulness-Based Stress Reduction
NCCN: National Comprehensive Cancer Network
PSA: Prostate-Specific Antigen
PTGI: Posttraumatic Growth Inventory
RCT: Randomized Controlled Trial
SPIRIT: Standard Protocol Items: Recommendations for Intervention Trials
SSSS: Satisfaction with Social Support Scale
TAU: Treatment As Usual
TNF: Tumour Necrosis Factor
WHOQOL-Bref: World Health Organization Quality of Life – Bref
